**Methods/Design:**

Cluster randomized, double-masked trial of children with and without uncorrected refractive errors or other eye conditions. Government schools in Hyderabad, India will be allocated to intervention (Peek) or comparator (standard programme) arms before vision screening. In the intervention arm Peek will be used for vision screening, SightSim images will be used in classroom teaching and will be taken home by children, and voice messages will be sent to parents of children requiring spectacles or referral.

In both arms the same criteria for recruitment, prescribing and dispensing spectacles will be used. After 3–4 months children dispensed spectacles will be followed up to assess spectacle wear, and uptake of referrals will be ascertained.

The cost of developing and delivering the Peek package will be assessed. The cost per child wearing their spectacles or accessing services will be compared.

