### Identification of potential participants and recruitment

In the intervention arm, field investigators in the school identified by the head teacher will first undertake classroom teaching using the SightSim images for all children aged 11–15 years, after training. A training manual will be developed to standardize the delivery. Field workers will be trained in each school to screen VA using the Peek vision screener app at the Snellen equivalent 6/9.5 level of VA, and children aged 11–15 years will be screened. To pass vision screening a child needs to correctly see four or five of five consecutive E optotypes. Once screening has been completed, all those who fail will be automatically referred to a visiting optometrist and will be refracted on the same day. Attendance will be checked against the data in the Peek software. After identifying children requiring spectacles each child will select a SightSim image of their choice from a range of images, which they will be asked to take it home to show their parents.

In the schools allocated to the comparator arm, trained field workers will screen VA using a standard card-based E optotype at the 6/9.5 level at 6 meters. To pass at the 6/9.5 level children need to correctly indicate the orientation of the E in at least four out of five optotypes. No health education materials or voice messages will be sent to the parents (Fig. 1).

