### Intervention and comparator arm

The intervention will be the Peek Acuity health education package. The comparator will be a standard school screening programme where no health education materials or messages are sent to parents (standard care) (Table 1).

**Table 1 Tab1:** An overview of the two arms of the trial

	Intervention arm	Comparator arm
Age group	11–15 years	11–15 years
Screening VA level	<6/9.5 in one or both eyes	<6/9.5 in one or both eyes
Method of screening	Peek E Acuity by field workers	E card optotype by field workers
Health education	• SightSim images for classroom teaching by field workers, after orientation i.e. for all children	None
	• Eligible children will select a SightSim image of their choice from a range of pre-tested images to take home to show their parents with wording in the relevant local language	
	• Personalized voice messages for parents in the relevant local language	
Refraction	Trained optometrist	Trained optometrist
Definition of significant RE	Same in both arms of the trial	Same in both arms of the trial
Dispensing criteria	Same in both arms of the trial	Same in both arms of the trial
Frame types	Same in both arms of the trial	Same in both arms of the trial
Delivery of spectacles	Same in both arms of the trial	Same in both arms of the trial
Assessment of primary outcome	Same in both arms of the trial	Same in both arms of the trial

*VA* visual acuity, *Peek* Portable Eye Examination Kit, *RE* refractive errors

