### Randomization

A list of schools where the head teachers has given permission will be prepared in India (PM) and each school will be allocated a unique ID. All clusters will be randomized at once so allocation concealment will not be an issue. The schools will be randomized using a web-based randomization service (Sealed Envelope Ltd. 2016. Simple randomisation service [Online]). Available from: https://www.sealedenvelope.com/simple-randomiser/v1/ [Accessed 3 Jan 2017])

The schools will be randomly allocated to intervention or comparator arm, stratified by size, i.e. the number of children enrolled at the school between the age 11–15 years. To reduce contamination, schools will be allocated to the intervention and control arm and not individual children, and study schools will not be closer than 10 km to minimize contact between children in the different arms of the trial. Recruitment bias will be unlikely because all children who fail screening i.e. who have a VA of less than 6/9.5, will have similar procedures thereafter, i.e. refraction, dispensing spectacles or referral, apart from the health education intervention, which will be applied after recruitment. Figure 1 is a flowchart showing a child’s journey and the activities involved from screening, to deciding whether they are eligible for recruitment, then randomization and follow-up.

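### The assurance that recruitment bias is unlikely conflicts with the procedures: in intervention schools the classroom lesson precedes screening and recruitment

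*Protocol article*

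**What the plan says.** All places are in the protocol article.

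- **Randomization.** The argument opens "Recruitment bias will be unlikely because all children who fail screening" and then have similar procedures, "apart from the health education intervention, which will be applied after recruitment". The same section describes Figure 1 as following the child "from screening, to deciding whether they are eligible for recruitment, then randomization and follow-up".
- **Abstract, Methods/Design.** Schools are allocated to the "arms before vision screening".
- **Identification of potential participants and recruitment.** In intervention schools, field staff "will first undertake classroom teaching using the SightSim images for all children aged 11–15 years". They then "screen VA using the Peek vision screener app at the Snellen equivalent 6/9.5 level of VA", and those who fail are refracted the same day. Comparator schools get no lesson and are screened with an E card at the same level, with the same pass rule of at least four of five.
- **Table 1.** Screening in the intervention arm is "Peek E Acuity by field workers". The first entry under health education is "SightSim images for classroom teaching by field workers, after orientation i.e. for all children"; the others are the take-home image and the voice messages.
- **Data analyses, Primary outcome.** The main comparison is a risk difference adjusted for school. A separate analysis adjusting for degree of refractive error and other factors is planned only if the arms are imbalanced.

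**The concern.** When clusters are allocated before participants are identified, randomization balances schools but not the way children enter the analysis set. The protocol recognises this and offers one defence: that education comes after recruitment. If part of the education comes first, that defence does not describe the trial as it will be run.

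A child who has just been taught what uncorrected refractive error looks like may differ from an untaught child in readiness to be screened, in assent, or in how he or she responds to acuity testing and subjective refraction. All of these help decide who is dispensed spectacles and so who is counted for the primary outcome. If such children also differ in their inclination to wear spectacles, part of the observed difference in wear would reflect who was recruited rather than the education.

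**Working it through.** **1. Order of events in an intervention school, as the sections give it**

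| Step | Where stated | Arm-specific? |
|---|---|---|
| School allocated | Abstract, Methods/Design | – |
| SightSim lesson to all children aged 11–15 | Identification and recruitment; Table 1 | Yes, intervention only |
| Screening at 6/9.5, pass at 4 of 5 | Identification and recruitment | Test differs: app or card |
| Refraction, two-line criterion | Inclusion criteria; Table 1 | Same |
| Take-home image | Identification and recruitment | Yes, after identification |
| Voice messages | Identification and recruitment | Yes, after spectacles or referral |

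One of three education components lies before screening and recruitment; two lie after. Without qualification, the Randomization sentence is true of two and false of one.

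**2. Reach of the assurance.** It starts from children who fail the screen, so it says nothing about who fails. The shared refraction and prescribing criteria remove false positives in both arms. They cannot recover a child whom one test passed wrongly.

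**3. The plan's own figures.** These reproduce and are not in dispute.
- Two proportions, 60% and 80%, two-sided 5%, 90% power, continuity-corrected: 119 per arm. 119 × 1.5 = 178.5; 178.5 / (1 − 0.20) = 223.1, rounded up to 224, against 225 stated.
- 17,300 × 0.026 = 449.8, against 450 stated. One yield is thus assumed for both screening methods.

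**4. Scale, on assumed inputs only.** Let a share s of true cases be mild, with wear probability a in mild and b in other cases, chosen so that overall wear is 60%. Suppose one arm's entry route (test, assent or test response) loses an extra fraction m of mild cases. With no education effect, that arm's wear rate becomes

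[s(1 − m)a + (1 − s)b] / [s(1 − m) + (1 − s)].

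| s | a | b | Shift at m = 10% | Shift at m = 50% |
|---|---|---|---|---|
| 0.5 | 0.50 | 0.70 | 0.53 points | 3.33 points |
| 0.4 | 0.45 | 0.70 | 0.63 points | 3.75 points |
| 0.4 | 0.30 | 0.80 | 1.25 points | 7.50 points |

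Example, last cell: (0.20 × 0.30 + 0.60 × 0.80) / 0.80 = 0.675, against 0.600.

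For comparison, the effective number per arm is 225 × 0.8 / 1.5 = 120, and the standard error of the difference at 60% in both arms is √(2 × 0.24 / 120) = 0.063, or 6.3 points. The assumed shifts run from under a tenth of a standard error to a little over one. The sign depends on which arm loses more mild cases, and the document does not say.

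**5. Flowchart sentence.** Eligibility followed by randomization cannot be squared with allocation before screening, nor with the statement in Randomization that all clusters are randomized at once.

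**The case against.** Several points on the other side have weight.

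- *The sentence may mean only the education given to children who fail screening*, that is, the image and the messages. That is a possible intention, but the wording is unqualified and Table 1 files the lesson under health education. The text still needs correcting.
- *Part of the willingness route is closed.* Under Consent, children whose parents opted out but who ask to be screened on the day are not recruited. Under Exclusion criteria, children can receive spectacles without joining the trial, so the lesson gives little reason to assent to research. The parental information sheets are not described as differing by arm. This stands. What remains is refusal of screening or assent by children whose parents did not opt out, and responses during testing.
- *Safeguards exist.* Inter-observer agreement studies for acuity screening and refraction, a conditional adjusted analysis and CONSORT cluster reporting are planned. They help, but no app-against-card comparison is stated and the adjustment depends on seeing imbalance.
- *Peek screening is openly part of the intervention arm.* This stands. A reader might infer that the different tests contradict the Randomization sentence and must be made the same. They do not contradict it, because the sentence speaks only of what happens after a failed screen. Using one test is a choice about what to compare.
- *The flowchart sentence is loose description.* Agreed; the figure is not shown, and other text makes the order clear. It is a wording correction.

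**Conclusion.** The contradiction is established from the text alone: the lesson is health education, it is given before screening and recruitment in one arm only, and the protocol's stated reason for discounting recruitment bias is that education comes afterwards. The primary analysis, adjusted only for school, does not protect against differential entry.

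A reader might go further and infer that the whole intervention precedes recruitment, that staff knowledge of the arm is stated, or that the result will be biased by a definite amount. The document supports none of these. Two of three components follow identification. That screening staff know the arm is a reasonable inference from their tasks, not something the protocol says. No comparative performance of the two tests, and no effect of the lesson on assent or testing, is given. The range of 0.5 to 7.5 points rests entirely on assumed inputs and shows scale only; size and direction are unknown.

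**What to change.** 1. In intervention schools not yet visited, give the SightSim lesson after screening, refraction, assent and recruitment, so that the statement about timing becomes true there.
2. Withdraw the statement that recruitment bias is unlikely. Say instead that children are identified after allocation, that the screening test differs by arm, and in which schools the lesson came first.
3. Correct the description of Figure 1 so that randomization precedes screening.
4. Report by arm the numbers enrolled, screened, failed, eligible and recruited, with presenting acuity and refractive error.
5. Carry out the adjusted analysis that includes degree of refractive error whether or not imbalance is seen. It addresses differences in severity, not unmeasured motivation, so it complements item 4 and does not replace it.

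The cost is a reordering in the field manual, some rewording and one extra table. Recruitment began on 4 January 2017 and was ongoing at submission, so schools already visited will have had the lesson first. The order used in each school must be recorded and the change reported as a protocol modification.

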### Primary outcome

The primary outcome is defined as the proportion of children who are wearing their spectacles at an unannounced visit to the school 3 to 4 months after delivery of the spectacles. A new field worker will be recruited and trained to collect the primary outcome data who will be masked to the hypothesis and intervention arm. Spectacle wear will be ascertained using the four categories defined by Wedner [18] where categories 1 or 2 below define spectacle wearing, and categories 3 or 4 as non-spectacle wearing: (1) wearing the spectacles at the time of the unannounced visit, (2) not wearing the spectacles at the time of the visit but have them at school, (3) not wearing the spectacles at the time of the visit but said they are at home, and (4) not wearing the spectacles at the time of the visit as they are broken or lost.

### Secondary outcome

Uptake of referral to Pushpagiri Eye Institute, which will be assessed 4–5 months after screening.

### Other outcomes

At follow-up, each child not wearing their spectacles will be asked why they are not wearing them. Children wearing spectacles will be asked why they are wearing them. They will be asked if there is a second reason. Their response will be written down verbatim by field workers and coded afterwards, with reasons for non-wear likely to fall into the following categories: (1) never received them, (2) lost, (3) broken or scratched, do not like wearing them because (4) they were teased, or (5) appearance, or (6) headache or eye strain; (7) parents do not like the child to wear them, (8) did not notice an improvement in vision i.e. no benefit and (9) other, which will be specified.

The costs of developing the Peek education package, and for delivering both arms of the trial, will be determined using standard costing methods and data from Peek software developers. The cost per child wearing their spectacles at follow-up will be calculated and compared between arms.

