### Purpose

The purpose of this cluster randomized trial is to evaluate whether a health education package for teachers, parents and children (aged 11–15 years), delivered using Peek increases spectacle wear at 3 to 4 months and uptake of referral of children identified with other eye conditions.

The trial will also assess the cost of developing and delivering the Peek health education intervention and the cost of dispensing and delivering the spectacles in both arms of the trial. The cost per child wearing their spectacles at follow-up will be compared between the two arms of the trial.

The hypothesis is that the proportion of children wearing spectacles 3–4 months after they were given their spectacles is higher in schools allocated to the innovative Peek educational package than in schools randomized to the standard programme. The uptake of referrals is also anticipated to be higher in the schools allocated to the Peek educational package than those randomized to the standard programme.

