### Sample size calculation

A superiority margin of 20% was chosen to balance the anticipated higher costs of developing and delivering the Peek package. We estimate that we will need a study size of 450 children (225 in each arm) to detect a difference of 20% in spectacle wear between the intervention and comparator arm, assuming approximately 60% of children in the control arm will be wearing spectacles at follow-up, with a 95% confidence interval and 90% power. We have adjusted the sample size calculations for clustering using data from our previous study (unpublished) to estimate a design effect of 1.5. We have increased the sample size by 20% to allow for loss to follow-up. A total of 17,300 children will need to be screened to recruit 450 children for this trial. The communities are stable and few study children are expected to leave the school during the school year.

This will detect a 20% difference in spectacle wearing, determined using the sampsi command in Stata Statistical Software version 14 (StataCorp, College Station, TX, USA).

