#### Other outcomes

Reasons for non-spectacle and spectacle wear will be compared between the two arms of the trial, after categorizing their responses.

Data on the cost per child wearing their spectacles at follow-up will only be analysed should the difference in spectacle wear be 20% or greater in the intervention arm.

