## Discussion

This trial is designed to evaluate whether a health education package for teachers, parents and children delivered using innovative mobile phone technology (Peek) increases spectacle wear at 3 to 4 months, as well as the uptake of referral of children identified during vision screening with other eye conditions. We will also assess the cost of developing and delivering the health education intervention in the intervention arm of the trial, and the cost of dispensing and delivering the spectacles in both arms of the trial. We will compare the cost per child wearing their spectacles at follow-up in both arms.

The Government of India recognizes the importance of correcting RE in children as they are included in the national programme for child health, called Rashtriya Bal Swasthya Karyakram (RBSK), and the National Program for the Control of Blindness. The health of schoolchildren is also recognized by international health experts, policy makers, governments and international agencies as contributing to child development, learning and socio-economic development. This includes FRESH (Focus Resources on Effective School Health) whose partners include Education International; Partnership for Child Development; UNESCO; UNICEF; the World Food Programme; the World Health Organization and the World Bank. Results of this project will, therefore, be of relevance to FRESH and local, national and international agencies.

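### The planned cost result compares each arm's average cost per wearing child, which does not give the cost of an additional wearer and compresses the contrast about fourfold at the design rates

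*Protocol article*

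**What the plan says.** The article names the same economic measure in four places.

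- Abstract, Methods/Design: "The cost per child wearing their spectacles or accessing services will be compared".
- Purpose: "The cost per child wearing their spectacles at follow-up will be compared between the two arms of the trial".
- Other outcomes, where outcomes are defined: "The cost per child wearing their spectacles at follow-up will be calculated and compared between arms".
- Discussion: "We will compare the cost per child wearing their spectacles at follow-up in both arms".

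Under Data analyses, Other outcomes, this analysis is conditional. The cost data "will only be analysed should the difference in spectacle wear be 20% or greater in the intervention arm".

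The Sample size calculation section gives the reasoning that links cost to effect: "A superiority margin of 20% was chosen to balance the anticipated higher costs of developing and delivering the Peek package". It sets the comparator rate by "assuming approximately 60% of children in the control arm will be wearing spectacles at follow-up". With the 20% difference, the design point is 60% against 80%.

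No section mentions a difference in cost between arms, a cost per additional wearer or an incremental ratio. No cost amounts are given.

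**The concern.** An average cost per wearer divides everything spent in an arm by everyone wearing spectacles in that arm. At the design rates, 60 of every 80 wearers in the Peek arm (three in four) would be expected to wear spectacles without the package. Dividing by all 80 spreads the added cost over children whose behaviour it did not change.

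The question implied by choosing a margin to offset higher cost is a different one: what does each wearer gained through Peek cost? A planner who reads the gap between two averages as the answer gets a figure that is too close to the control average. If Peek is dear, added wearers look cheaper than they are. If Peek is cheap, the saving looks smaller than it is.

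Costs are a stated aim in the Abstract, the Purpose and the Discussion, and they shaped the target difference, so the summary should answer the question the design poses.

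**Working it through.** **Inputs.** Comparator wear p0 = 0.60 and Peek wear p1 = 0.80 (Sample size calculation). The analysis condition is a wear difference of at least 20% (Data analyses, Other outcomes). Costs are not given, so let C be the comparator cost per child dispensed spectacles and d the extra cost per child with Peek. Every value of d below is an assumption.

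**The plan's own figure.** There is no cost figure to reproduce. The one computed figure tied to these rates is 225 children per arm. A two-sided 5% test of 60% against 80% with 90% power and continuity correction needs 119 per arm. Then 119 × 1.5 = 178.5, and 178.5 / 0.8 = 223.1, or 224 per arm. (Multiplying by 1.2 instead gives 215.) This supports reading the 20% as percentage points, but says nothing about cost.

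**Formulas.**

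- Control average: A0 = C / p0
- Peek average: A1 = (C + d) / p1
- Cost per additional wearer: I = d / (p1 − p0)

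**Relation between them.** Since d = A1·p1 − A0·p0, it follows that I − A0 = p1(A1 − A0) / (p1 − p0). If A1 is x% above A0, then I is x · p1/(p1 − p0) % above A0. At 0.60 and 0.80 the factor is 0.80/0.20 = 4. It contains no cost term, so it holds whatever C and d turn out to be.

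**Worked values at 60% against 80%** (A0 = C/0.6 = 1.67C, I = 5d):

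| Added cost d (assumed) | Peek average A1 | A1 against A0 | Additional wearer I | I against A0 |
|---|---|---|---|---|
| 0.1C | 1.1C/0.8 = 1.375C | −17.5% | 0.1C/0.2 = 0.5C | −70% |
| 0.33C | 1.67C | 0% | 1.67C | 0% |
| 0.5C | 1.5C/0.8 = 1.875C | +12.5% | 2.5C | +50% |
| 0.6C | 1.6C/0.8 = 2.0C | +20% | 3.0C | +80% |
| 1.0C | 2.0C/0.8 = 2.5C | +50% | 5.0C | +200% |

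In each row the last percentage is four times the middle one.

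**Break-even.** A1 = A0 when (C + d)/0.8 = C/0.6, that is d = C/3. Above one third, I exceeds both averages, so they understate the cost of an additional wearer. Below one third, I is under both averages, so they overstate it.

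**Larger effects that also meet the condition.** With p0 = 0.60, the factor is 0.85/0.25 = 3.4 at 85% wear and 0.90/0.30 = 3 at 90%. The compression eases with a larger effect but remains.

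The Abstract extends the comparison to children accessing services. The article gives no design rates for that outcome, so no size can be worked out there.

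**The case against.** Several points on the other side are fair.

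- **The averages do not mislead on direction.** The Peek average is above the control average exactly when an additional wearer costs more than the control average. A reader might infer that the planned comparison could favour the wrong arm on that yardstick. The algebra rules this out. Only the size is affected.
- **The error is not always understatement.** A reader might infer that averages flatter Peek. They do so only if Peek adds more than one third to the cost per child; below that they do the reverse. The article gives no costs, so neither case can be called the likely one.
- **Small effects are screened out.** A reader might picture wear rising only to 65% at an extra 0.3C, where the Peek average is 2.0C but an additional wearer costs 0.3C/0.05 = 6.0C. That is a 5-point difference, and under the 20% condition no cost per wearer would be analysed. The case carries no weight here.
- **No decision rule is attached.** The article does not say that Peek will be judged cost-effective on this comparison, and it places the result among the other outcomes, below the primary and secondary ones. The 20% margin already sets a requirement on the gain in wear. That covers the effect half of the question, but it does not state what the gain costs.
- **A condensed article may leave economic methods elsewhere.** It does not say whether the averages will be compared as a difference or a ratio, and costing detail may well sit in a fuller document. But the quantity to be compared is named four times, so this is a stated choice and not a gap.
- **The ratio is recoverable.** If arm costs and wearing proportions are all published, a reader can derive it. The article does not commit to reporting the ratio or its uncertainty.

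**Conclusion.** The point holds as a matter of measure and scale. The named economic result is not the quantity implied by the rationale for the 20% margin. At the protocol's own 60% and 80%, it shows one quarter of the proportional contrast between an additional wearer and the control average. That factor depends only on the two wearing rates. The absolute figures (for example 3.0C against averages of 1.67C and 2.0C, or 0.5C against 1.67C and 1.375C) rest on assumed cost ratios. The direction of the error depends on whether Peek adds more or less than one third to the cost per child, which the document does not let a reader judge.

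The consequence is limited to a conditional, lower-ranked outcome. The primary comparison of spectacle wear, the sample size and the conduct of the trial are not affected. The change is worth making because the planned summary does not answer the economic question that the design raises.

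**What to change.** In the Abstract (Methods/Design), the Purpose, both Other outcomes sections (outcome definition and Data analyses) and the Discussion, define the comparison as the difference in mean cost per child divided by the difference in wearing proportion, that is, the incremental cost per additional wearer. Keep the arm averages as description.

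Show the result with and without development costs. Development is a one-off sum, so its share of d depends on how many children it is spread over.

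Give uncertainty that respects clustering by school. If costs are recorded by school, resample whole schools. The article does not say that they are. Otherwise, hold costs fixed and carry the cluster-adjusted confidence interval for the wear difference, already planned for the primary outcome, through the ratio. If that interval reaches zero, report that the ratio has no finite upper limit.

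The cost is revised wording and a small amount of extra analysis. The costs and wearing data are already planned, and recruitment and sample size do not change.
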